#### Methods for Additional Analyses

In an exploratory and hypothesis-generating mode, potential moderators for Deprexis treatment effects will be examined. Generalized linear mixed models with robust maximum likelihood estimation will be used to model continuous outcomes (eg, changes in psychosocial functioning outcomes and depressive symptoms), and logistic models will be used to model changes in dichotomous outcomes (eg, significant change: ≥50% improvement in scores) over time. *Participant* will be entered as a random effect (ie, random intercepts). Each potential moderator will be examined in a separate model for changes in primary outcomes (QIDS-SR-16, WHODAS-II, and SDS). Each model will include main effects for the potential moderator and time (before treatment, after treatment, and follow-up), 2-way interactions (moderator×time and time×treatment condition), and a 3-way interaction (moderator×time×treatment condition). To prevent spurious associations, the α value will be Bonferroni corrected [65]. A variable will be considered a moderator of treament effects if there is a significant 3-way interaction (moderator×time×treatment condition) after treatment or at 8-week follow-up.

#### Definition of Analysis Population Relating to Protocol Nonadherence and Any Statistical Methods to Handle Missing Data

Consistent with CONSORT (Consolidated Standards of Reporting Trials) recommendations [66], aim 2 analyses will be conducted across four groups: (1) the intention-to-treat group, which includes data from all randomized participants, regardless of treatment adherence or attrition; (2) the per-protocol group, which consists of participants who are considered treatment adherent, defined as ≥60 minutes of Deprexis use (which is consistent with previous research [29]); (3) the high-engagement group, which consists of participants who demonstrated strong treatment uptake, defined as ≥90 minutes of Deprexis use (this cutoff is approximately 1 SD below the mean for the treatment-adherent group in the general population Deprexis RCT); and (4) the completer group, which consists of participants who complete both baseline and posttreatment assessments. In the intent-to-treat group, the *Amelia II* (version 1.8.2) package in R [67] will be used to impute missing data with an expectation-maximization and bootstrapping algorithm. All available variables will be used to impute missing data, and the number of imputed datasets will be based on the proportion of missing data.

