### Sample Size

#### Aim 1

In determining the sample size for qualitative studies, the key goals are to develop case-oriented perspectives, select participants with a range of characteristics and perspectives, and achieve saturation (ie, the point at which subsequent interviews fail to produce new themes) [56]. Research indicates that typically, saturation is reached with 12 to 16 interviews. As we are also obtaining qualitative data on veterans who did not adhere to the treatment (approximately 23% of the sample), we increased our recruitment target slightly to 16 to 20 veterans to allow for a sufficient sample of veterans who completed Deprexis treatment, as well as those who terminated treatment early (ie, did not complete the posttreatment or follow-up questionnaires).

#### Aim 2

Effect sizes in the general population Deprexis RCT for participants with mild to moderate depression (QIDS-SR-16 score <21) ranged from Cohen *d*=0.65 to Cohen *d*=0.90. Some evidence suggests that effect sizes for psychological interventions may be smaller for veterans [57]; therefore, we estimate that effect sizes are at least medium (Cohen *d*=0.50) for measures of functioning and large (Cohen *d*=0.80) for depressive symptoms. To achieve 0.8 power at an α of .05, a total of 102 participants need to be recruited. Accounting for 23% attrition over time, we will randomize 132 participants at baseline. In the general population trial, approximately 57% (n=213) of the randomized participants were high engagers (>90 min), and effect sizes were slightly higher in the high engager group (Cohen *d*>0.67) than in the overall sample. Thus, we expect to be adequately powered for analysis in this subgroup.

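### The intention-to-treat imputation does not provide for a moderator×condition term; without one, the exploratory moderator estimates shrink toward zero by about the share of outcomes missing

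*Protocol article*

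**What the plan says.** Two sections of the protocol article have to be read together.

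- **Methods for Additional Analyses** sets the decision rule for aim 2b: "A variable will be considered a moderator of treament effects if there is a significant 3-way interaction", at posttreatment or at the 8-week follow-up. Each moderator has its own mixed model with a random participant intercept, fitted by maximum likelihood. The significance level is Bonferroni corrected, with no divisor given. The section calls this work exploratory and states no interaction size and no power.
- ***Definition of Analysis Population Relating to Protocol Nonadherence and Any Statistical Methods to Handle Missing Data*** (below: the missing-data section) runs the aim 2 analyses in four groups. For the intention-to-treat group only, it names Amelia II, which "will be used to impute missing data with an expectation-maximization and bootstrapping algorithm". On the inputs it says: "All available variables will be used to impute missing data". Product terms and imputation separately by arm are neither included nor excluded.

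The Sample Size section gives the expected extent of missing data: "Accounting for 23% attrition over time, we will randomize 132 participants at baseline".

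**The concern.** Amelia II treats all supplied columns as jointly normal, so each missing score is drawn from a regression that is linear in those columns. Given condition, moderator and earlier scores, that regression has one moderator slope shared by both arms, unless a moderator×condition column is supplied or the arms are imputed separately. A product is not a collected variable; somebody has to construct it. On the natural reading of the input rule, the imputed records therefore carry no moderation, whatever the observed records show. Lengthening the list of collected variables does not cure this.

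At stake is the purpose of aim 2b, which is to find candidate moderators. Real ones would be missed more often in the intention-to-treat set. The completer set is not imputed, so its moderator estimates would be systematically larger, and that gap could be misread as an effect of attrition.

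**Working it through.** **1. Inputs.** From Sample Size: 132 randomized, 23% attrition. The two figures agree: 102/(1 − 0.23) = 132.5, against the stated 132. The 102 itself is matched by a one-sided t test (d = 0.50, 51 per arm, power 0.806; two-sided 0.706), which is a separate matter and is not used here. The article gives no power figure for aim 2b, so there is none to reproduce. For the Bonferroni divisor I assume 11: the Outcomes section lists six demographic variables plus PTSD severity, comorbidity, credibility, study support and Deprexis use (6 + 5 = 11).

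**2. Algebra.** Let β be the true difference between arms in the moderator slope and f the fraction of outcomes imputed. Observed records show β; imputed records show 0. With missingness unrelated to the moderator and equal by arm, the completed data give

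(1 − f)·β + f·0 = (1 − f)·β.

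For β = 0.60: f = 0.23 gives 0.77 × 0.60 = 0.46; f = 0.12 gives 0.88 × 0.60 = 0.53. The relative shrinkage does not depend on β or α.

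**3. Simulation.** Assumptions: 66 per arm, outcome SD 1, visit correlation 0.5, standard normal baseline moderator, 23% of scores missing completely at random, 20 bootstrap normal imputations pooled by Rubin's rules. The test is moderator×condition on change from baseline.

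- Estimate without the product: mean 0.45 for a true 0.60. In a second, independent simulation the ratio to the truth was 0.74–0.79 across effect sizes. With the product the bias disappears (0.60 for a true 0.60).
- Rejection under no moderation at nominal 5%: 1.7% and 2.4% in the two simulations without the product; 5.8% with it.
- Power, with β per SD of the moderator:

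| α | β | Observed cases | Imputed, no product | Imputed, with product | Loss from omitting product (points) |
|---|---|---|---|---|---|
| .05 | 0.195 | 19% | 10% | 19% | 9 |
| .05 | 0.341 | 36% | 20% | 38% | 18 |
| .05 | 0.488 | 66% | 46% | 68% | 22 |
| .05 | 0.628 | 87% | 70% | 87% | 17 |
| .05/11 | 0.347 | 15% | 5% | 16% | 11 |
| .05/11 | 0.494 | 34% | 14% | 35% | 21 |
| .05/11 | 0.640 | 62% | 31% | 65% | 34 |
| .05/11 | 0.780 | 82% | 54% | 85% | 31 |

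**4. Small interactions at α=.05/11.** Observed cases against imputation without the product: 4% against 2% for β = 0.2, and 9% against 3% for β = 0.3. At α=.05 the same two effects lose about 7 and 15 points.

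**5. Attrition that accrues.** Assume 12% missing at posttreatment and 23% at follow-up, with β = 0.60. At posttreatment power falls from 60% to 47% at α=.05/11 (13 points) and from 89% to 82% at α=.05 (7 points). At follow-up the loss is about 19 and 12 points. It is smaller than with 23% missing at both visits, because the posttreatment scores of later dropouts carry part of the moderation into their imputed follow-up scores.

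**The case against.** The strongest objection is that the defect is inferred. The missing-data section does not say that products are left out, and it could be followed to the letter with them included. Such detail is often left to an analysis plan, and this is a condensed article. This stands as far as wording goes: one cannot say that the protocol imputes without an interaction. It does not dispose of the point. The article fixes the engine, the inputs and the scope, and following them on their natural reading gives a worse moderator analysis than the mixed model already described.

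A reader might also infer a definite loss of 20 to 30 points of power. The documents do not support that, since they state no interaction size and no divisor. Losses of that size need large interactions. With a main effect of −0.5, β = 0.60 moves the treatment effect from −1.1 at one SD below the moderator mean to +0.1 at one SD above. They also need the strict divisor and 23% missing already at posttreatment, whereas the Sample Size section describes attrition over time. For small interactions at α=.05/11 power is low either way.

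Further limits stand. The aim is exploratory, and the error is conservative, so it creates no false moderators. Deprexis use has no TAU counterpart and lies outside the argument. The Measures section has veterans with no criterion A event skip the PCL-5 items, so that moderator and its product are missing by design for an unknown share.

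**Conclusion.** The concern holds in conditional form. As written, the intention-to-treat imputation does not secure the term that the aim 2b decision rule tests. If the term is absent, the interaction estimate for a baseline moderator shrinks by roughly the fraction of outcomes missing, and the test rejects about 2% of the time at nominal 5%.

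The shrinkage follows from the method and the missing fraction. The power loss does not follow from the documents and can only be given as a range under stated assumptions (missing completely at random, visit correlation 0.5, 23% missing): a few points for small interactions at α=.05/11, about 10–20 points at α=.05, and up to about 25–35 points for large interactions at α=.05/11. It is smaller at posttreatment if attrition accrues over time.

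Only the intention-to-treat version of aim 2b is affected. This argument gives no reason to doubt the aim 2a comparison or the completer analysis. Severity is minor to moderate.

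**What to change.** In the missing-data section, state that the aim 2b intention-to-treat models are fitted directly by likelihood to all observed outcomes of all randomized participants. The mixed model under Methods for Additional Analyses already allows for outcomes missing at random, so no imputation of outcomes is needed there.

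If Amelia II is kept for aim 2b, impute once per moderator with the moderator×condition product as an added column. Condition is known for everyone and most baseline moderators for nearly everyone, so the column is almost complete. The PCL-5 is the exception and needs its own rule, because of the skipped items.

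The cost is a sentence of wording, or one imputation run per moderator under the alternative. The downside is that aim 2b would not use the same imputed datasets as aim 2a. Participants, data collection and sample size are unchanged.

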### Dissemination of Results

Several manuscripts are planned to align with the various study aims. In addition, results will be presented at research conferences, and summaries will be drafted for media releases. Author eligibility and order will be determined by the study PI.

### Oversight and Monitoring

#### Composition of the Data Monitoring Committee, Its Role, and Reporting Structure

The data safety monitoring board (DSMB) will be responsible for safeguarding the interests of trial participants, assessing the safety and efficacy of the interventions during the trial, and monitoring the overall conduct of the clinical trial [68]. The DSMB will provide recommendations about stopping or continuing the clinical trial. To contribute to enhancing the integrity of the trial, the DSMB may formulate recommendations relating to the selection, recruitment, and retention of participants; their management; improving adherence to protocol-specified regiments; and procedures for data management and quality control. The DSMB will consist of at least 3 members, all of whom are independent of the trial. Any protocol deviations or unanticipated problems involving risks to participants or others will be reported to the DSMB within 5 days, as well as to the IRB, and summarized in the study progress report and submitted during continuing review.

#### Interim Analyses

No interim analyses are planned.

#### Adverse Event Reporting and Harms

In cases of unanticipated problems involving risks to participants or others or apparent serious or continuing noncompliance with federal regulations for the protection of research participants or the requirements or determinations of the IRB, a written report will be prepared for submission to the central IRB and DSMB within 5 business days of notification. The report will include a brief narrative summary of the event as well as a determination of whether a causal relationship existed between the study procedures and the event, whether the informed consent should be revised because of the event, and whether all enrolled participants should be notified of the event. All team meetings will begin by asking whether any such events have occurred.

#### Frequency and Procedures for Auditing Trial Conduct

Yearly auditing will be conducted by an IRB member who is independent of the study and its investigators. This is to ensure that the study is compliant with the protocol and is meeting the standards of human participant research.

### Ethical Considerations

The protocol has been approved by the Central Texas Veterans Affairs Healthcare System IRB (protocol 2024-001). Any changes to the study protocol will be promptly communicated to relevant stakeholders.

A waiver of informed consent will be obtained for the completion of the eligibility screen. Informed consent will be obtained for the remainder of the study procedures. A watermarked paper copy of the informed consent will be included with the study recruitment letter. An electronic version of the consent form will be included in the Qualtrics eligibility survey. Veterans will be asked to review the consent form, and they will be asked whether they have any questions or concerns. Veterans who indicate that they have questions or concerns will be contacted by telephone by the research technician. Once all questions and concerns are responded to, the research technician will verbally ask whether the veteran is still interested in the study and if the veteran answers in the affirmative will send a link to DocuSign consent via encrypted email. Veterans who indicate that they do not have questions or concerns will be asked in the Qualtrics eligibility screen whether they are interested in participating in the study. If they answer in the affirmative, they will be sent a link to DocuSignconsent via encrypted email.

No participant data will be released in any form unless the investigators or study personnel are mandated to do so by law (eg, because of risk to self or others). All study data will be kept in accordance with VA guidelines, which require that electronic and paper data be kept for the duration of the study and for 6 fiscal years thereafter (for details on data storage and disposition, refer to VA Records Control Schedule 10-1 [69]). Participants will be assigned a study ID, which is linked to identifying information in a password-protected spreadsheet, which is stored behind the VA firewall. Study personnel who have access to study data will receive training in confidentiality policies and procedures.

All IRB-approved study team members may have access to participant-level data pending approval from the study PI. The full protocol will be available at the discretion of the study PI.

## Results

This study was funded in May 2024. Data collection is anticipated to take place between October 2024 and April 2029. Currently, 4 participants have been recruited into this study. The results are expected in November 2029.

## Discussion

### Summary

Research examining computer-delivered interventions in veterans lags behind that conducted in general population samples. This study will gather the qualitative experiences of veterans with a computerized intervention and will be the first RCT of a self-guided, computerized intervention for depressive symptoms and functional impairment in veterans. The results from the described study will demonstrate whether the positive results in general population trials of computerized interventions generalize to the veteran population. Furthermore, we broaden the target population of these types of interventions by including veterans with subthreshold symptoms of depression. The described trial has an explicit focus on functional outcomes because there is evidence that symptomatic recovery and functional improvements do not consistently improve in tandem after mental health interventions. Deprexis has previously been associated with significant improvement in disability and well-being; however, these were secondary outcomes. This study centralizes and significantly expands the assessment of psychosocial functioning across domains.

Depressive symptoms, independent of comorbid trauma symptoms, are an important driver of functional impairment and suicidality in veterans. When depressive symptoms co-occur with PTSD, these symptoms often persist after trauma-focused treatments. Thus, depressive symptoms should be an urgent target of intervention in veterans, even in the context of complex comorbid conditions. There is evidence that the depression treatment gap commonly described in community samples also exists for veterans who receive their care at VA facilities [20]. Various reasons for the existence of this treatment gap have been suggested, and it seems likely that multiple individual, logistical, and institutional barriers may prevent veterans with depressive symptoms from receiving appropriate care. Cost-effective, accessible computerized interventions would broaden the reach of depressive treatments available within the VA system.

Importantly, the VA system is an appropriate site for testing an intervention such as Deprexis. The broad screening for depressive symptoms that occurs at all VA clinics (ie, outside of specialty mental health clinics) and the integrated mental health record allow for the timely identification of veterans presenting with relatively mild depressive symptoms. There is an opportunity to prevent chronicity and disease progression by focusing treatment on mild to moderate depressive symptoms. There is evidence that Deprexis may be especially effective for individuals with lower depressive symptom severity [53]. Our long-term vision is that brief, computerized interventions such as Deprexis can be integrated in a stepped-care approach, providing rapid intervention for veterans with mild to moderate depressive symptoms, while reserving resource-intensive treatments such as face-to-face psychotherapy for individuals with severe symptomatology.

Alongside the aforementioned strengths, this study has several limitations. The choice of a TAU control group is a relatively weak comparator. Follow-up studies comparing Deprexis to active treatment conditions would provide further evidence for the relative impact of the intervention. All assessments administered in this study are self-report questionnaires, which are prone to certain types of bias (eg, desirability bias). If the efficacy of Deprexis is supported in this trial, examining whether change also generalizes to other assessments, such as ecological momentary assessment or tracking, may be merited. Relatedly, because no clinical interviews are conducted, we are not able to assess the presence or absence of clinical diagnoses. Finally, use will be closely monitored in this trial, which may not be feasible in clinical settings. Automating use reminders may be an important step to promote successful uptake in the VA system.

### Conclusions

Despite the aforementioned limitations, we believe that the described study will provide much needed initial evidence for the effectiveness of computerized interventions broadly and Deprexis specifically for veterans presenting with depressive symptoms and functional impairment. The results obtained in this study could inform the rollout of targeted computer-delivered interventions that address common barriers to mental health care in veterans. This is especially pertinent given that demand for VA behavioral health care outpaces supply, resulting in increased outsourcing of behavioral health care in the form of community care referrals [70]. Building a diverse arsenal of psychosocial interventions, including computerized interventions, potentially allows more veterans to receive behavioral health care within the VA system. Furthermore, giving veterans additional mental health care options could improve overall engagement with treatment [71]. We believe that the results of this study could potentially extend and advance routine care for veterans with depressive symptoms, which is an essential step toward closing the treatment gap and providing the highest quality care for veterans with complex mental health needs.

## Abbreviations

BDI-II: Beck Depression Inventory–Second Edition
CONSORT: Consolidated Standards of Reporting Trials
DSMB: data safety monitoring board
IIP-SC: Inventory of Interpersonal Problems–Short Circumplex Form
IRB: institutional review board
ISEL-SF: Interpersonal Support Evaluation List–Short Form
MDD: major depressive disorder
PCL-5: posttraumatic stress disorder Checklist for Diagnostic and Statistical Manual of Mental Disorders, Fifth Edition
PDSQ: Psychiatric Diagnostic Screening Questionnaire
PHQ: Patient Health Questionnaire
PI: principal investigator
PTSD: posttraumatic stress disorder
QIDS-SR: Quick Inventory of Depressive Symptomatology–Self-Report
QLS: Quality of Life Scale
RCT: randomized controlled trial
SDS: Sheehan Disability Scale
TAU: treatment-as-usual
VA: US Department of Veterans Affairs
WHODAS-II: World Health Organization Disability Assessment Schedule II
